### The intervention: guided online intervention i-Sleep for insomnia

The online intervention i-Sleep, developed at the Vrije Universiteit Amsterdam ([name]), is based on a mixture of self-help materials, research literature and interviews with patients. The treatment consists of online lessons and includes the elements that are commonly incorporated in face-to-face CBT-I [19–23]. Initially the treatment consisted of 6 lessons. Based on the first trial on i-Sleep [42] we decided to combine the first two lessons (on psycho-education and sleep hygiene) into one because most patients were already familiar with (part of) this information. The topics during the five lessons are explained in Table 1. The intervention is offered with online guidance from a coach. The aim of the feedback is to comment on exercises, clarify information and motivate the patient to persist in carrying out the course and the requested behavioral changes [44]. The coach responds to every session the patient completes. We advise patients to do one lesson every week but they can take some more time if needed. However, during this study, coaching will stop 8 weeks after patients received login details even in case patients do not finish the entire treatment.

**Table 1 Tab1:** The session of online treatment i-Sleep

Session	Content
1	Psycho-education, and sleep hygiene.
2	Stimulus control and sleep restriction: patients are taught to use the bedroom only to sleep and to get in and out of bed at the same time every day. Furthermore they are asked to restrict this the time in bed to the average amount of night-time sleep. The initial sleep window prescribed is based on sleep diary parameters over 7 nights, with a minimum of a 5 hour sleep window. When sleep efficiency (percentage of time spent in bed that the person is asleep) is below 85 %, time in bed is restricted. Above 85 %, the sleep window can be lengthened. Position of the sleep window is as patients prefer (going to bed later or getting up earlier). Daytime napping is discouraged. If unavoidable, no longer than 30 minutes and not after dinner. Sleep restriction will be continued in session 3, 4 and 5 according to need.
3	Relaxation exercises and exercises to minimize worrying.
4	Dysfunctional cognitions about sleep are addressed: the basics of cognitive therapy are explained and the most common erroneous ideas about insomnia are discussed.
5	Summary and plan for the future.

Patients in the intervention condition will receive guidance from a psychological wellbeing practitioner (PWP) in each general practice, usually a (psychiatric) nurse. We will provide training for the PWP in CBT-I as well as in providing online feedback. The training will consists of a 1.5 hour workshop, guided practice with the online course and feedback training. PWPs will be supervised by the first author (TZ) and an experienced CBT psychologist. Patients in both conditions are also allowed to receive care-as-usual from their GP or the PWP.

### Care-as-usual group

We will provide the participating GPs in our study with a written version of the Dutch insomnia guidelines [32]. The core message of the guideline is formulated as: (1) the preferred insomnia treatment is non-pharmacological, (2) the GP might consider medication in exceptional situations, and only short term, (3) the preferred treatment for short-term sleep problems is psycho-education and information about sleep hygiene, (4) for longer term sleep problems the preferred treatment is a combination of stimulus-control, sleep restriction, relaxation and structured exercise [32]. We will not interfere with the care that the GPs offer their patients. After online data collection, we will extract information on consumption of GP-care and prescription of medication from GP electronic records. Also, we will inquire from patients themselves how many nights was medication used in the last week using the sleep diary.

### Assessments

Four assessments will take place: at baseline (T0), 8 weeks post-treatment (T1), 6- (T2) and 12-month (T3) follow-up. For an overview of the measurements see Table 2. Questionnaires will be administered online. Additionally, participants will receive an actigraphic watch and a sleep diary by mail at all assessments. Patients are asked to wear the actigraphic watch for 7 days while also filling out the sleep diary for these same days [48]. Additionally, data extracted from the electronic medical records in general practice will be used to assess consumption of care and prescription of sleep medication, up to 12 months follow-up.

**Table 2 Tab2:** Measurements and instruments at different point of assessment

Measurement	Instrument	Baseline (T0)	T1, T2 and T3 (at 8, 26 and 52 weeks)
Background characteristics	n/a	X	-
History of insomnia	n/a	X	
Alcohol use	AUDIT	X	X
Insomnia severity	ISI	X	X
Anxiety and depression	HADS	X	X
Daytime insomnia consequences	Espie et al., 2012	X	X
Daytime functioning	WSAS	X	X
Fatigue	FSS	X	X
Quality of life	EQ-5D-5 L	X	X
Healthcare utilization & work absenteeism	TiC-P	X	X
Treatment satisfaction	n/a	-	T1
Actigraphy	Actigraph GT9X Link	X	X
Sleep diary	Consensus diary	X	X
Sleep medication	n/a	X	X

AUDIT: Alcohol Use Disorders Identification Test; ISI: Insomnia Severity Index; HADS: Hamilton Anxiety and Depression Scale; WSAS: Work and Social Adjustment scale; FSS: Fatigue Severity Scale; EQ-5D-L: EuroQoL; TiC-P: Trimbos and iMTA questionnaire on Costs associated with Psychiatric Illness

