### Randomization

After inclusion patients are randomized by an independent researcher using random sequence block randomization (blocks of 2, 4 or 6), stratified by whether or not they have used sleep medication in the past 4 weeks and by individual PWP, on a 1:1 ratio. After inclusion of a patient the independent researcher reveals the next randomization outcome. Due to the nature of the study, blinding of the researchers, PWPs or patients is not possible.

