### Adverse effects

We will investigate potential adverse effects. Adverse effects are defined as (1) worsening of sleep symptoms, and (2) accidents. Adverse effects could be a result of the insomnia disorder itself, but also potentially of the sleep restriction exercise in i-Sleep. We will assess the primary outcome measure in order to identify clinically significant deterioration, e.g. exacerbation of insomnia severity from pre- to post-treatment (ISI change score of 7 points or more [50]. Additionally, we will ask participants at post-test and follow-up 1 and 2 whether they experienced a) falling incidents, b) traffic accidents, c) any other negative events that they feel are related to fatigue/sleepiness. Participants unavailable for post-test and/or follow-up due to dropout will be asked these questions via e-mail. The occurrence of adverse effects in the intervention and in the care-as-usual condition will be compared.

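### Accidents are ascertained only by patient reply, and the planned GP-record extraction, which needs no reply, is not used to supplement them

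*Protocol article*

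**What the plan says.** The Adverse effects section sets the scope: "Adverse effects are defined as (1) worsening of sleep symptoms, and (2) accidents". It names the sleep restriction exercise as a possible cause. For accidents it states that "we will ask participants at post-test and follow-up 1 and 2 whether they experienced a) falling incidents, b) traffic accidents", and adds a third item, "any other negative events that they feel are related to fatigue/sleepiness". For those lost to assessment, "Participants unavailable for post-test and/or follow-up due to dropout will be asked these questions via e-mail". It then commits to a comparison: "The occurrence of adverse effects in the intervention and in the care-as-usual condition will be compared".

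On blinding, the Randomization section says: "Due to the nature of the study, blinding of the researchers, PWPs or patients is not possible".

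The GP record appears in three places. The Care-as-usual group section says that "we will extract information on consumption of GP-care and prescription of medication from GP electronic records". The Assessments section, which sets a 12-month limit, says that "data extracted from the electronic medical records in general practice will be used to assess consumption of care and prescription of sleep medication". The Cost measures section lists the number of consultations with GPs and well-being practitioners, plus prescriptions. None of the three lists accidents, injuries or the reason for a consultation.

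**The concern.** Both channels for accident data need the patient to answer. Those asked by e-mail have already become unavailable for a study whose questionnaires are administered online. The Background says that side effects of CBT-I come mainly from greater fatigue under sleep restriction. A patient who leaves the study for that reason could be at higher risk of an accident and also less likely to report one. Only the intervention arm is assigned i-Sleep before month 6, so such losses could differ between arms.

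What is at stake is the between-arm comparison of accidents, which the article presents as part of a strength of the study (examining possible negative effects). Accidents are likely to be few, so a handful of unreported events could matter. The GP record is the one planned source that does not depend on a reply.

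**Working it through.** **The plan's own figure.** The Sample size section gives d = 0.50, 80% power, alpha 0.05 (two-sided assumed) and 20% dropout, leading to 80 per arm. A two-sample normal formula gives 63 per arm, and 63 / (1 − 0.20) = 78.75, so 79. Starting from 64, 64 / 0.80 = 80. The stated 160 reproduces and is not in dispute.

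**How many patients depend on the e-mail.** 0.20 × 80 = 16 per arm, or 0.20 × 160 = 32 in total. This is the only quantity below that comes from the document. Reply rates are assumed.

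**Patients with no accident data, and the worst-case effect.** With reply rate r, the missing number per arm is m = 16 × (1 − r). If all missing patients in one arm had an accident and none in the other did, the risk difference would shift by m / 80.

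| Assumed reply rate | Missing per arm | Largest shift in risk difference |
|---|---|---|
| 0% | 16 | ±20 points |
| 25% | 12 | ±15 points |
| 50% | 8 | ±10 points |
| 75% | 4 | ±5 points |

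These are outer bounds, not expected biases.

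**Share of accidents missed within one arm.** If dropouts have k times the accident risk of completers (assumed), the share is 0.2k(1 − r) / (0.8 + 0.2k).

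- k = 1, r = 0.6: 0.08 / 1.0 = 8%
- k = 3, r = 0.4: 0.36 / 1.4 = 26%
- k = 4, r = 0.2: 0.64 / 1.6 = 40%

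This is an undercount within an arm. If it is equal in both arms, the risk ratio is unchanged. At an assumed 5% risk, an arm of 80 has 0.05 × 80 = 4 accidents, and losing 26% of them is about one event.

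**Differential reporting.** Suppose true risks are equal, and accidents are reported with 90% sensitivity in one arm and 75% or 60% in the other (assumed). The observed risk ratio is then 0.90 / 0.75 = 1.2 or 0.90 / 0.60 = 1.5, instead of 1.0. The document gives no basis for the direction.

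**Precision with complete data.** For an assumed 15% versus 5%, power is 0.56 with 80 per arm and 0.47 with 64 per arm. The comparison is imprecise whichever source is used.

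**What the record can and cannot add.**

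| Component | Could the GP record help? |
|---|---|
| Falls and traffic accidents that led to care and were recorded | Yes, without a patient reply |
| Falls and traffic accidents with no consultation | No |
| Other events the patient attributes to fatigue or sleepiness | No, this is the patient's own judgement |
| Worsening of sleep (ISI rise of 7 points or more) | No |

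**The case against.** The strongest reply is that nothing here is stated wrongly. Both arms are asked the same questions at three time points, dropouts are pursued, and the arms are compared. The e-mail asks a few short items, whereas the full assessment is a questionnaire battery, a week of diary and a week of actigraphy, so it is a real safeguard. A condensed article may also leave the detailed extraction form to the full protocol. Most of this stands, and it makes the point an improvement and not the correction of an error. Even so, the article itself says what the record is for in three places, and accidents are in none of them.

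Some stronger readings are tempting but are not supported:

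- *The record of every randomised patient will be opened.* The article describes extraction without restriction, but never says that it covers all patients or dropouts.
- *The missing data and bias are avoidable.* They are only partly so. Consulting and recording are themselves unblinded, and the practitioner who coaches i-Sleep works in the same practice.
- *Patients who stop i-Sleep are lost.* Stopping treatment is not leaving the study. The Statistical analysis section keeps all data regardless of treatment completion.
- *The undercount favours i-Sleep.* Differential dropout is only supposed. Patients told to restrict sleep might instead report more sleepiness-related events.
- *8% to 40% of accidents will be missed.* Those figures rest on assumed reply rates and risks, and the top value needs both extremes together.

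The objection on cost also stands in part. Searching all incoming hospital letters with a strictly masked extractor would be chart review, and should not be required.

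**Conclusion.** The point holds in a limited form. Accidents are a defined adverse effect with a planned between-arm comparison, yet they are ascertained only by reply from unblinded patients. A planned source that needs no reply is unused for them. Using it would make the comparison less dependent on response for accidents that reached the practice, but it would neither replace self-report nor resolve the low precision.

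The gain cannot be quantified from the document. The document supports only the figure of about 16 of 80 patients per arm who depend on the e-mail, and that assumes the planned 20% dropout occurs equally in both arms. The rest depends on unknown reply rates, risks and differences between arms. The point concerns one part of a harm comparison. The primary analysis and the sample size do not change.

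**What to change.** When consultations are extracted from the GP record, also record the date and whether the contact was for a fall, injury or traffic accident. Do this for all randomised patients whose record is available under their consent, including those lost to follow-up. Report a supplementary comparison of medically attended accidents between arms, from inclusion to the six-month offer of i-Sleep to controls. Keep self-report as the main source. Mask the extractor to arm where this is feasible without extra staff. The Care-as-usual group, Assessments, Cost measures and Adverse effects sections need matching wording.

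The cost is some extra extraction time and a check that consent and ethics approval cover the item. No visit, questionnaire or procedure is added. The report should state that the count includes only accidents that led to care.

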### Primary outcome: insomnia severity

The primary outcome of the study will be insomnia severity as measured by the Insomnia Severity Index [49]. The ISI consists of 7 items scored on a 5-point Likert scale (0 = not at all, 4 = extremely) and scores range from 0–28, higher scores indicating more severe insomnia. The ISI assesses the nature, severity and the impact of insomnia. Previous research has indicated that the Insomnia Severity Index (ISI) is a valid and reliable instrument to quantify perceived insomnia severity and presents a clinically useful tool in screening as well as outcome measurement. It possesses adequate internal consistency (Cronbach’s alpha = .90), is sensitive to changes in perceived sleep difficulties over time [50] and has been validated for online use [51]. We use a community sample cut-off score of ≥10 to define clinical insomnia [50].

### Secondary outcomes

#### Questionnaires

Daytime consequences suffered due to insomnia will be measured using 6 items on the different domains mentioned in the DSM-5 diagnosis of insomnia disorder: energy, relationships, mood, concentration, productivity, and sleepiness [52] rated on a 5-points scale at each assessment phase (0 = not at all affected through to 4 = very much affected).

Daytime functioning will also be assessed using the 5-item Work and Social Adjustment Scale [53]. Each of the five items measure a domain of functioning: work, home management, social leisure activities (i.e. with others), private leisure activities (i.e. individually) and ability to form and maintain close relationships with others. For each domain of functioning the score ranges from 1 through to 8, with higher scores indicating more severe disruption. The internal consistency of the WSAS ranges from Cronbach’s alpha 0.70 to 0.94 [53].

We will use the Fatigue Severity Scale [54], which consists of 9 items, to measure fatigue. Each item is scored on a 7-point Likert scale, ranging from 1 (strongly disagree) through to 7 (strongly agree). Higher scores indicate more severe fatigue. This scale has shown an excellent internal consistency and reliability (Cronbach’s alpha of 0.93; [55]).

The Hospital Anxiety and Depression Scale consists of 14 items which are scored on a 4-point Likert scale each. Seven items can be summed into a depression a score and the other half into an anxiety score. Higher scores represent more severe anxiety or depression [56]. The HADS is a reliable and valid instrument also in Dutch populations (Cronbach’s alpha of .88, [57]).

The Alcohol Use Disorders Identification Test questionnaire (AUDIT [58]), designed by the World Health Organisation to screen for excessive alcohol consumption, will be used to assess alcohol use, using a 5-point Likert scale (higher scores indicating more alcohol use and related issues). This instrument has a clear cut-off value, is often used and well validated [58]. The total score represents consumption level, dependence and present alcohol-related harm. We will use the standard cut-off of 8 to identify (but not exclude) heavy drinkers which has shown to have good sensitivity and specificity in detecting current social and medical problems related to alcohol.

The EuroQol questionnaire (EQ-5D-5 L) [59] will be used to measure health-related quality of life. Health states will be converted to utility scores using the Dutch EQ-5D-5 L tariff. Quality-adjusted life-years (QALYs) will be calculated by multiplying the utility score of a health state by the time spent in that health state. Transitions between health states will be linearly interpolated.

#### Diary and actigraphy

We will measure sleep estimates derived from both the consensus sleep diary and the use of wrist actigraphy. The sleep estimates are: Sleep Onset Latency (number of minutes it takes to fall asleep after going to bed), Sleep Efficiency (percentage of the total amount of time spent in bed that is spent asleep), Number of Awakenings, Wake After Sleep Onset (total minutes awake after sleep onset), Total Sleep Time and Sleep Quality (a number between 1 and 5 for each night). We will use the Dutch translation of the consensus sleep diary [60] with some minor text adaptations, achieved by consensus among a group of Dutch sleep researchers.

In addition to the subjective sleep evaluations gathered using the questionnaires and sleep diary, objective sleep data will be collected using actigraphy. Actigraphic watches, accelerometers recording motion over short epochs, are non-invasive small devices worn on the non-dominant wrist 24 hours a day. We will equip participants with an Actigraph GT9X Link provided by ProCare, under Actigraph Actilife 6 SmEnterprise licenses. The Actilife software (http://www.actigraphcorp.com/solutions-and-products/software/actilife/) will be used to extract the data from the actigraphic watches. We will use a validated script to calculate different sleep estimates: sleep period, total sleep time, clock time falling asleep, wake up time, percent sleep, wake after sleep onset, number of wake bouts, fragmentation and latency [48, 61]. We will compare the objective and subjective data.

### Cost measures

Healthcare utilization will be assessed in two ways. First we will use data derived from GP records. We will assess the number of consultations with GPs, and general well-being practitioners as well as medication prescriptions. Next, we will ask the patients themselves which other healthcare services they used (GP and other) and which sleep and other medication they took. For this we will use the TiC-P [62] (Hakkaart-van Roijen et al., 2002). The Short Form Health and Labour Questionnaire which is also part of the TiC-P will be used to measure absenteeism from paid and unpaid work, and presentism [62]. Healthcare utilization will be valued using Dutch standard tariffs [63]. Costs associated with lost productivity will be estimated according to the friction cost approach [64].

### Adverse effects

We will investigate potential adverse effects. Adverse effects are defined as (1) worsening of sleep symptoms, and (2) accidents. Adverse effects could be a result of the insomnia disorder itself, but also potentially of the sleep restriction exercise in i-Sleep. We will assess the primary outcome measure in order to identify clinically significant deterioration, e.g. exacerbation of insomnia severity from pre- to post-treatment (ISI change score of 7 points or more [50]. Additionally, we will ask participants at post-test and follow-up 1 and 2 whether they experienced a) falling incidents, b) traffic accidents, c) any other negative events that they feel are related to fatigue/sleepiness. Participants unavailable for post-test and/or follow-up due to dropout will be asked these questions via e-mail. The occurrence of adverse effects in the intervention and in the care-as-usual condition will be compared.

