### Inclusion and exclusion criteria

Patients aged 18 and over who turn to their GP for help with insomnia complaints are evaluated for eligibility. Inclusion criteria are assessed using a screening questionnaire (t0) and include: difficulty initiating or maintaining sleep for at least 30 minutes a night, for at least three nights a week, for at least three months, causing clinically significant distress and/or impairment in daily functioning, i.e. meeting criteria for a DSM-5 diagnosis of insomnia [1]. Exclusion criteria are: no access to the internet, inadequate proficiency in Dutch, meeting criteria of the diagnosis of sleep apnea (assessed by the GP and in the screening questionnaire using the Screening for Sleeping disorders [46], pregnancy or breast feeding during the trial, working in night shifts, psychological treatment in the last six months, being suicidal (assessed using 5 items from the MINI diagnostic interview [47]), and schizophrenia or psychotic disorder (“Have you been diagnosed with schizophrenia or psychosis?”, to which participants reply ‘Yes’ or ‘No’). Other comorbid psychological disorders and somatic diseases are allowed. The use of (sleep) medication is also allowed and tracked.

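### The only worsening criterion given, an ISI rise of 7 or more, cannot be met from a baseline of 22 or more or assessed without a post-test ISI, which dropouts are not asked for

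*Protocol article*

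**What the plan says.** The Adverse effects section names two components: "Adverse effects are defined as (1) worsening of sleep symptoms, and (2) accidents". For the first, the ISI is to be used to identify clinically significant deterioration, "e.g. exacerbation of insomnia severity from pre- to post-treatment (ISI change score of 7 points or more". This is introduced as an example, but no other criterion for worsening sleep is given.

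For the second, participants are asked at post-test and at both follow-ups "whether they experienced a) falling incidents, b) traffic accidents, c) any other negative events that they feel are related to fatigue/sleepiness". The next sentence deals with patients who are no longer being assessed: "Participants unavailable for post-test and/or follow-up due to dropout will be asked these questions via e-mail". The section ends by committing to compare adverse effects between the two arms.

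The section Primary outcome: insomnia severity fixes the scale: "The ISI consists of 7 items scored on a 5-point Likert scale", and "scores range from 0–28, higher scores indicating more severe insomnia". Entry under Inclusion and exclusion criteria is by symptoms, "i.e. meeting criteria for a DSM-5 diagnosis of insomnia", and sets no upper ISI limit.

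Statistical analysis states multiple imputation for Cohen's d. The cost-effectiveness section states it for cost and effect data. Neither mentions the deterioration count.

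**The concern.** The protocol expects that some harm will occur in patients who leave, and it plans to contact them. As written, that contact collects the accident-type questions but not the measure on which the first adverse-effect component depends. An analysis plan can choose denominators and imputation models, but it cannot recover answers that were never requested.

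The threshold also meets the top of the scale. The patients with the most severe insomnia at entry have no room to show a 7-point rise.

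This matters because the protocol itself names the sleep restriction exercise as a possible cause of adverse effects, and Strengths and weaknesses lists the examination of negative effects among the study's five major strengths. Both gaps can only remove worsening events from the observed count. The missing values are also missing primary-outcome values, so the same contact could serve two purposes.

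**Working it through.** **1. The plan's own figure.** Inputs from Sample size: d = 0.50, power 80%, alpha 0.05 (two-sided assumed, since sidedness is not stated) and 20% dropout. By the normal approximation, n per arm = 2 × (1.96 + 0.84)² / 0.50² ≈ 63, and 63 / 0.80 = 78.75, so 79. The t-based solution is 63.8, so 64, and 64 / 0.80 = 80. The stated 80 per arm (160 in total) reproduces and is not in dispute. At the planning rate, 0.20 × 160 = 32 patients drop out.

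**2. The ceiling.** The largest possible rise is 28 − baseline, and the criterion needs 28 − baseline ≥ 7, that is, baseline ≤ 21.

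| Baseline ISI | Largest possible rise | Can meet the criterion? |
|---|---|---|
| 20 | 8 | yes |
| 21 | 7 | yes, only by reaching 28 |
| 22 | 6 | no |
| 23 | 5 | no |
| 28 | 0 | no |

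**3. How many patients start at 22 or more.** The protocol gives no baseline ISI mean or SD. As an assumption, take a normal distribution rounded to whole scores and restricted to 10–28, with mean 15 to 19 and SD 3 to 5. The share at 22 or more, with the number out of 160, is:

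| Mean | SD 3 | SD 4 | SD 5 |
|---|---|---|---|
| 15 | 1.6% (3) | 5.7% (9) | 10.8% (17) |
| 17 | 6.7% (11) | 13.3% (21) | 18.8% (30) |
| 19 | 20.2% (32) | 26.2% (42) | 29.7% (47) |

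**4. Both gaps together.** Suppose all 32 dropouts lack a post-test ISI and dropout is independent of baseline. The share in whom the criterion cannot register is then 1 − (1 − c) × 0.80, where c is the share at 22 or more. For c = 1.6% this is 21% (34 of 160). For c = 29.7% it is 44% (70 of 160). Overlap is counted once. These are patients out of the criterion's reach, not missed events; the documents give no deterioration rate from which to count missed events.

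**5. What the ceiling does to the comparison.** Let p₁ and p₀ be the rates of a 7-point rise among patients starting at 21 or less. If all patients form the denominator and c is the same in both arms, the observed rates are (1 − c)p₁ and (1 − c)p₀. The difference shrinks by the factor (1 − c), while the ratio is unchanged. The ceiling alone therefore favours neither arm.

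**6. What a missing post-test does.** Let r be the probability that a patient who has worsened still supplies a post-test ISI, and q the same probability over all patients in the arm.
- With all randomised patients as denominator, the observed rate is p × r. It is too low whenever r < 1, and the ratio of arms is distorted if r differs between them.
- With assessed patients as denominator, the observed rate is p × r / q. It is correct only if r = q, that is, if missing the post-test is unrelated to worsening.

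The documents give neither r nor q by arm.

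**7. Which patients are affected.** The criterion runs from baseline to post-treatment. A patient lost only at 6 or 12 months has a post-test ISI and can register, and so can one who stops the course but completes the 8-week assessment. Only patients without a post-test ISI are out of reach, so 32 is an upper figure at the planning rate.

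**The case against.** The strongest reply has five parts.

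- **The 7-point rise is only an example.** This is correct, and the sleep diary and actigraphy collected at every assessment could also show worsening, whatever the baseline ISI. The section does not name them as harm measures, however, and they come from the same assessments that dropouts miss.
- **Harm in dropouts is not ignored.** This also stands. The third e-mailed question is open to any negative event the patient links to fatigue or sleepiness, and GP records are extracted up to 12 months. Neither source yields an ISI change.
- **Randomisation balances the ceiling.** This stands too, as step 5 shows. The ceiling lowers the count and the absolute difference without favouring an arm.
- **Denominators and missing-data rules belong in an analysis plan that is not shown.** That is fair for the reporting part. It does not answer the collection part, because the protocol states what dropouts will be asked.
- **Dropouts have already failed to return an online ISI, and a longer e-mail might lower replies to the safety questions.** This is a real trade-off. Placing the ISI items last limits it. No reply rate can be taken from the documents, so no gain is claimed in figures.

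A reader might infer that harm as a whole is undercounted, or that nobody who drops out can be recorded as worse. The documents support neither. Only the ISI-worsening component is affected, only patients without a post-test ISI are missed, and whether events are actually lost depends on data not yet collected.

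**Conclusion.** The point holds as a limited gap in measurement. It is exact that no patient with a baseline ISI of 22 or more can meet the one worsening criterion given, and that the protocol admits such patients. It follows from the text that the e-mail to dropouts does not include the ISI, so a patient without a post-test ISI has no observed value for that criterion. ISI worsening can therefore be undercounted.

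Bias between the arms is conditional: it arises if missing the post-test is related to worsening or differs by arm. A flat claim that the comparison is biased towards no harm would go further than the documents allow.

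The size cannot be derived. At the planning rate at most about 32 of 160 patients lack a post-test ISI. The share starting at 22 or more runs from about 2% to 30% under the assumed distributions, and its low end is negligible. The missing post-test is the weightier part, since it can be mended only at data collection; the ceiling needs only an added line of reporting.

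**What to change.** - Add the seven ISI items to the e-mail already planned for patients who miss an assessment, placed after the safety questions.
- Record the date of each answer and flag those given outside the assessment window.
- Use these answers both in the between-arm comparison of deterioration and in the primary ISI analysis.
- Report by arm the number with baseline ISI of 21 or less who rise by 7 or more, with the number of such patients as denominator. Report separately any ISI worsening among those with baseline 22 or more.

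The cost is seven items in an existing contact and one more row in the harms table. The downsides are a slightly greater burden on people who have already withdrawn effort, some off-window values, and possibly a few incomplete replies.
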